### Demographic Information

The following demographic information will be collected from the participants: age, gender, university enrollment status, indigenous status, work history, previous history of burnout, current engagement in psychological therapy or other treatment, and self-rating (5-point Likert scale) of current physical health, diet, and self-care behavior.

### Primary Outcome: Burnout

We will assess burnout using the 3-factor Maslach Burnout Inventory–General Survey for Students [77]. This 16-item self-report questionnaire assesses the degree to which participants are experiencing each of the following burnout components: *Exhaustion,* stress; *Cynicism,* attitude; and *Academic Inefficacy,* achievement. The Maslach Burnout Inventory scale is valid [2], and the reliability of the Maslach Burnout Inventory–General Survey for Students has been demonstrated among a sample of medical students from the United States [76].

### Secondary Outcome: Well-being

Reducing burnout risk via the enhancement of PF processes is the primary goal of the skill development program, however, it is also known that PF tends to improve well-being outcomes. This is an important goal because psychological health is not only reflected by the absence of adverse outcomes but also by the presence of well-being [78]. A secondary goal of the intervention program is to facilitate improved well-being among the participants. We will assess well-being using the Mental Health Continuum–Short Form [78]. This 14-item self-report questionnaire assesses the frequency of well-being experiences during the previous month. The scale has demonstrated validity [78], reliability [75,79], and sensitivity to changes in web-based intervention studies [80].

### Process Outcome: PF

We will assess PF and psychological inflexibility (PI) using the Multidimensional PF Inventory–Short Form [47]. This 24-item self-report questionnaire assesses the frequency of each PF and PI experience during the previous 2 weeks. In addition to global PF and PI scores, individual subscale scores can be calculated for each of the 6 PF and 6 PI processes. The scale has demonstrated validity [53] and reliability [81] and is responsive to changes over time [47].

### Depression, Anxiety, and Stress

Depressive symptoms, anxiety, stress, and general negative affectivity will be screened as secondary outcomes for two key reasons: (1) for comparison purposes with previous similar studies and (2) to explore whether these factors are related to engagement in the intervention as has been observed in previous studies [82]. We will assess these symptoms using the Depression Anxiety and Stress Scale-21 [83]. This valid and reliable 21-item self-report questionnaire assesses the degree of symptoms of depression, anxiety, and stress during the previous week and a general negative affectivity factor [84].

### Engagement Data

We will assess the following behavioral engagement metrics using app use data.

#### Recruitment

The number of participants who enroll in the study during the recruitment period will be assessed.

#### Adherence

The proportion of recruited participants who meet adherence requirements, defined as the completion of stage 1 and engagement in at least four skill activities during stage 2 (individualized vs nonindividualized analyses only), will be assessed.

#### Attrition

We will assess attrition at all stages of the program: enrolled but did not sign-up to use the app, did not complete T_1_ assessments, did not complete brief educational module, did not complete stage 1, did not complete adherence requirements for stage 2 (individualized vs nonindividualized analyses only), and did not complete T_2_ assessments.

#### App Engagement Frequency

The frequency of participant engagement with components of the app during stage 2 will be assessed using the following: app log-ins, check-in assessments completed, skill activities completed, and skill activities completed per log-in.

#### Individual Skill Activity Feedback

Following the completion of each stage 2 skill activity, participants will be asked to indicate whether they *liked* the activity by selecting either a thumbs-up (like) or thumbs-down (dislike) icon.

### Intervention

#### PF Model: ACT Intervention

This study will deliver an ACT PF skills training intervention in written and audio formats via a web-based app. ACT facilitates the development of individual PF skills for nonclinical populations, promoting and facilitating actions that support individual well-being [52,67]. Rather than defining uncomfortable internal experiences (eg, thoughts, emotions, and physical sensations) as *symptoms* that need to be changed or eliminated, ACT focuses on altering the way individuals relate to these internal experiences [46,85] and empowering them to respond in ways that are more adaptive in their own lives [86]. This is accomplished through activities that normalize challenging internal experiences as well as training individuals to strengthen present-moment awareness, recognize the influence of their internal experiences over their actions, learn to alter unworkable responses to these internal experiences, and develop more flexible behavioral repertoires that are consistent with their personally chosen values [45,46,85,86].

ACT is conceptually well defined and links its interventions to the mechanisms through which it purportedly elicits change (ie, the 6 PF processes and their corresponding inflexibility processes) [87]. The components of an ACT intervention include the following: present-moment awareness (mindfulness), cognitive defusion, self-as-context, acceptance, values, and committed action.

Two clinical psychologists (first and second authors: [name]) with extensive training and experience with ACT interventions and the PF model designed the app intervention. The piloting of the intervention among a small cohort of medical students at the University of Newcastle indicated high acceptability and usability.

#### Intervention Stages

All participants will complete a brief introductory session that provides education about burnout, psychological well-being, and PF skills (approximately 10 minutes). Participants will then be randomly allocated to the waiting list, individualized intervention, or nonindividualized intervention arm. Participants who are allocated to the individualized and nonindividualized groups will have access to the 2-stage app for 5 weeks.

Stage 1 (Learn the Concepts) presents a conceptual overview of each PF process and provides a framework through which participants can understand the rationale and potential personal relevance of the skills they will be practicing in stage 2. During stage 1, participants are given opportunities to practice each PF skill set. Depending on whether participants choose to complete these optional skill activities, the completion time for stage 1 is approximately 30 to 60 minutes and can be completed over more than one sitting. The completion of stage 1 will unlock access to stage 2.

During stage 2 (Learn the Behaviors), participants will have access to *on demand* PF skills training. They will be asked to complete a check-in assessment each time they access the app, to assess which PF process they are currently experiencing the most difficulty with. For the individualized intervention arm, a participant’s check-in assessment response at each log-in will be used to individualize their intervention. That is, participants will receive access to training in whichever skill they report having the most difficulty with in that moment. Participants will be directed to a dashboard that gives them access to all the available skill activities for their identified PF process (eg, if a participant identifies that they are having difficulty attending to the present moment, they will be presented with the present-moment awareness dashboard). Participants may then select an activity or have the app select a random activity for them from within the targeted PF skill set. This method is similar to one adopted in a recent study assessing a web-based ACT intervention for anxiety and depression [75]. For the nonindividualized intervention arm, check-in assessment responses *will not* be used to select a targeted PF skill set for the participant’s training during that session. Rather, participants will be directed to any of the PF process dashboards at random.

Upon the completion of a stage 2 skill activity, participants will be asked if they would like to complete another activity. If they select *yes,* those in the individualized group will return to the dashboard of the PF process identified at check-in and may repeat the aforementioned activity selection process. Participants in the nonindividualized group will be presented with another random activity. Participants may complete as many activities as they choose, but will be asked to complete at least four stage 2 skill activities during their 5-week period of access to the app.

Each of the 6 PF dashboards includes 20 brief (2-7 minutes) experiential skill-building activities, resulting in a total of 120 activities available in stage 2. The inclusion of this number of activities was guided by previous studies, indicating that 28 activities were too few [88] and 136 activities were sufficient [75]. An example activity for each skill set is provided in Multimedia Appendix 1, along with the activity aims as they relate to the PF processes.

### App Engagement

Previous piloting of this intervention by our research team indicated that self-reported acceptability by medical students did not necessarily correspond with regular behavioral engagement with the app. Pilot findings showed high engagement in stage 1 but lower than expected engagement in stage 2. Facilitating ongoing user engagement is a known challenge for developers of app-based mental health interventions [89]. The current version of the intervention incorporates the pilot study participants’ feedback and suggestions to enhance engagement for the RCT. This includes ensuring that participants are clear about what to expect throughout the intervention, providing clear indicators of progress and achievement, providing opportunities for personally relevant interactive learning and self-reflection, delivering in-app reminder notifications (push notifications), and delivering information in multiple forms where possible (eg, written and audio) to accommodate individual learning preferences and situational conditions. The app will also encourage engagement through the provision of positive reinforcement when a participant completes certain activities or completes a particular number of activities (eg, an achievement badge acknowledging their commitment and the benefits of practice).

### Data Analysis

Descriptive and inferential statistics will be used to describe demographic, outcome, and app engagement data. To assess hypotheses 1 to 3, modeling to examine treatment efficacy with follow-up outcomes will be performed, using mixed models (with appropriate distribution and link function), including a random intercept for participants to account for repeated measures. Descriptive analyses will be performed for use data obtained from the app platform to assess engagement, including engagement frequency and retention and adherence rates.

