#### PF as an Individual Protective Factor and Intervention Target

There is increasing evidence that PF skills can function as protective individual resources regarding burnout and well-being. Recent research has demonstrated associations between individual PF processes and work-related stress [39,41], burnout [55-58], and well-being [39,41,58,59]. PF processes account for unique variance in burnout symptomatology [41,60] and well-being [53]. These demonstrate predictive validity related to long-term workplace mental health [61] and show stronger and more consistent relationships with burnout and work-related well-being than do traditional organizational factors, such as job control and workload [41,56]. Interestingly, PF has also been shown to influence the degree to which employees are able to notice, engage with, and benefit from changes made to organizational burnout risk factors (eg, job control) [61], providing further support for the value of implementing individual interventions in conjunction with organizational interventions. PF skills have been shown to mediate relationships between stressors (eg, COVID-19–related stress) and well-being outcomes [62]. In nonmedical populations, interventions targeting individual components of the PF skill set demonstrate efficacy relating to reducing work-related stress and burnout [63-69], improving well-being [70], and improving coping in response to work-related stressors [63]. ACT interventions that provide training in the full PF skill set have been shown to reduce workplace stress and improve well-being [39].

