### PF as a Mechanism of Burnout and Well-being Change

One of the pitfalls of many cognitive behavioral intervention studies is that they deliver training packages that demonstrate efficacy regarding outcomes of interest, without identifying the mechanisms through which these interventions exert their effect [40]. Understanding the processes that underlie an intervention’s efficacy can facilitate greater intervention precision [40]. For example, knowing that PF is a mechanism of change for medical student burnout would open up opportunities for the delivery of other interventions that may improve these skills and facilitate the efficient delivery of the intervention *dose* needed to produce meaningful improvements in PF to reduce a particular individual’s burnout risk. Demonstrating the efficacy of an intervention through its impact on mediating processes is particularly important when seeking to prevent a distal adverse outcome. This provides opportunities to deliver interventions that strengthen these mediating skill sets among at-risk individuals (eg, medical students) before the emergence of adverse outcomes (eg, burnout).

Expectations of the efficacy of the current ACT intervention regarding burnout and well-being are based on the assumption that the training will help medical students use PF skills as an adaptive coping resource. This assumption is supported by previous mediation studies that demonstrated that ACT interventions influence burnout and well-being outcomes by improving an individual’s PF skills [39,58]. PF processes may also mediate longer-term burnout risk as demonstrated in intervention studies where improvements in PF processes reduced the subsequent risk of burnout development [55]. To assess the assumptions of our intervention and improve the rigor of our efficacy assessment, we will explore whether PF is a mechanism of change for any observed burnout and well-being intervention effects.

Hypothesis 2 states the following: on the basis of the theoretical background provided, we hypothesize that changes in burnout and well-being outcomes will be mediated by changes in PF.

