### Sample Size

We conducted a power analysis to determine an appropriate sample size for a repeated measures multivariate analysis of variance (3 groups; measuring 2 time points [baseline and after the intervention]; high correlation between pre- and postintervention measures, 0.6). The calculation allowed for a small but still clinically meaningful effect size (0.25), given that this is the most conservative approach. For power of 80% and Cronbach α of .05, the total required sample size is 117 (39 per intervention arm). We allow for an attrition rate of up to 30% and set our target recruitment sample size at 153 participants (51 per intervention arm).

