### Data Collection Tools and Procedures

Data will be collected at two time points: T_1_ (baseline) and T_2_ (following the completion of the app-based intervention, commencing 5 weeks after baseline).

Study data will be collected via the app, which will record participant responses to questionnaires as well as app use data. Table 1 shows the administration time points for each outcome measure.

**Table 1 table1:** Outcome measures and administration time points.

Outcome	Assessment	Baseline (T_1_)	After the intervention (T_2_)	Every log-in (stage 2)
Demographics	Demographics	✓		
Burnout	Maslach Burnout Inventory–General Survey for Students	✓	✓	
Well-being	Mental Health Continuum–Short Form	✓	✓	
Psychological flexibility and psychological inflexibility	Multidimensional Psychological Flexibility Inventory–Short Form	✓	✓	
Depression, anxiety, and stress	Depression Anxiety and Stress Scale-21	✓	✓	
Current psychological flexibility difficulty	Check-in assessment			✓
Activity acceptability	Like or dislike			✓

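### The analysis assigned to hypothesis 2 estimates total treatment effects only, so it cannot show whether psychological flexibility mediates change in burnout and well-being

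*Protocol article*

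**What the plan says.** Hypothesis 2, in the Introduction section on PF as a mechanism, reads: "we hypothesize that changes in burnout and well-being outcomes will be mediated by changes in PF". The same section introduces it with "we will explore whether PF is a mechanism of change for any observed burnout and well-being intervention effects".

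The Data Analysis section names one method by hypothesis number: "To assess hypotheses 1 to 3, modeling to examine treatment efficacy with follow-up outcomes will be performed, using mixed models", "including a random intercept for participants to account for repeated measures". It describes the purpose as treatment efficacy and does not mention mediation, a mediator model or an indirect effect.

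On measurement, "Data will be collected at two time points": baseline and after the intervention. Table 1 places PF, burnout and well-being at both. The PF questionnaire "assesses the frequency of each PF and PI experience during the previous 2 weeks", so follow-up PF covers much the same period as the follow-up outcomes.

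The abstract's Conclusions and the Discussion section on contributions both draw practical consequences from a positive mediation finding, chiefly that preventive programs could target PF.

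**The concern.** A mediation claim needs two links and their product: arm to change in PF (a), change in PF to change in outcome given arm (b), and a × b. Hypothesis 1 already lists PF as an outcome, so the stated model supplies a. Nothing in the section supplies b or the product.

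An analyst who follows the text would have arm effects on PF and on burnout and no test of the link between them. The shortest improvised step would be to add PF to the same random-intercept model. That has its own problem: a single PF slope mixes differences between students with changes within a student, while hypothesis 2 concerns only the changes. At stake is the reliability of a finding that the article would use to recommend PF as a target for prevention.

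**Working it through.** The document gives no mediation figure to reproduce. Its only design calculation, 117 participants (39 per arm), contains no mediation parameter and serves here only as a sample size.

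**Inputs from the document.** 39 per arm, so 78 app and 39 waiting list; "high correlation between pre- and postintervention measures, 0.6". On a unit-variance scale I take this as a stable part with variance 0.6 and a time-specific part with variance 0.4, for PF and for burnout.

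**Assumptions, not in the document.** The app raises PF by 0.5 SD; the total effect on burnout is -0.5 SD; the stable parts of PF and burnout correlate at r between 0 and -0.7. The article reports PF-burnout associations but not their size.

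**Step 1: what the stated model returns.** Total effect = direct effect + a × b.
- No mediation: -0.50 + 0.5 × 0 = -0.50.
- Full mediation: 0 + 0.5 × (-1.0) = -0.50.

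Simulated arm-by-time coefficients were -0.50 in both cases. The stated analysis cannot tell the two apart.

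**Step 2: adding PF as one unsplit covariate, true PF effect zero.** Split each student's two values into sum/√2 and difference/√2. The between-person slope is (2 × 0.6 × r)/(2 × 0.6 + 0.4) = 0.75r, and the within-person slope is 0. The random-intercept model averages the two, each weighted by PF variance over residual variance. For r = -0.5 (between-person slope -0.375), the solution is:
- between residual variance: 1.6 - 2(0.2022)(0.6) + 1.6(0.2022²) = 1.423; weight 1.6/1.423 = 1.125
- within residual variance: 0.4(1 + 0.2022²) = 0.416; weight 0.4/0.416 = 0.961
- slope: 1.125 × (-0.375)/(1.125 + 0.961) = -0.20

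The spurious indirect effect is 0.5 × (-0.20) = -0.10, or 20% of the total effect. Simulation agrees: slope -0.20, and the arm-by-time term shrinks from -0.50 to -0.39. At 2,000 per arm the slope is still -0.20, so this is bias and not small-sample noise.

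Share of simulated trials (2,000 per setting) declaring mediation, meaning a and b both significant at 5%, when the truth is none:

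| Stable r | PF unsplit, 39 per arm | PF unsplit, 51 per arm | Within-person change only, 39 per arm |
|---|---|---|---|
| 0 | 5% | 5% | 4% |
| -0.3 | 36% | 48% | 4-5% |
| -0.5 | 71% | 85% | 4-5% |
| -0.7 | 81% | 89% | 4-5% |

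A separately coded simulation at 39 per arm gave 35%, 68% and 80% for the last three rows of the unsplit model.

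**Step 3: limits of the change-based model.** It removes stable confounding only. Suppose the time-specific parts of PF and burnout share a cause with correlation w, still with no PF effect. The variance of a change score is 2 × 0.4 = 0.8.
- Path a: SE = √[0.8(1/78 + 1/39)] = 0.175; z = 0.5/0.175 = 2.85; probability of significance = Φ(2.85 - 1.96) = 0.81.
- Path b: expected slope w; SE = √[(1 - w²)/114], where 114 = 117 - 3.

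| w | z for b | P(b significant) | × 0.81 | Simulated |
|---|---|---|---|---|
| -0.1 | 1.07 | 0.19 | 0.15 | 15% |
| -0.2 | 2.18 | 0.59 | 0.48 | 47-48% |
| -0.3 | 3.36 | 0.92 | 0.75 | 73% |

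PF and the outcomes are self-reported at the same two time points, so a shared time-specific cause such as an assessment period or current mood is plausible. Its size is unknown.

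**The case against.** The strongest reply is that this is a short section of a journal article, and that mediator models and intervals belong in a fuller protocol or analysis plan that is not shown. Mixed models are also a class: one for PF by arm and one for outcome on arm and PF could together support a mediation analysis, and PF split into person-mean and within-person parts stays inside that class. This part stands: the data and the model family are adequate, and it would be wrong to infer that the trial cannot answer hypothesis 2. It does not remove the point, because the article does not leave the method open. It assigns hypothesis 2, by number, to treatment-efficacy modeling.

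A reader might also infer that the trial will report false mediation at the rates above. The documents do not support that. Nowhere do they say that PF will be entered as an unsplit covariate; the correlations and the 0.5 SD PF effect are assumptions; and at r = 0 there is no inflation. The rates are a warning about one way of filling the gap.

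Nor do the documents support reading the change-based analysis as a clean causal test, as the third step shows.

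Finally, the article says it will explore the mechanism, burnout is the primary outcome, and the Discussion words its mediation conclusions conditionally. That limits the severity.

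**Conclusion.** The point holds for the stated method: a treatment-efficacy mixed model with a random intercept yields total effects, and these are the same (-0.50 in the worked example) with no mediation and with full mediation. This needs no assumption about effect sizes.

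The false-mediation rates, about 36% to 81% at 39 per arm, are conditional on PF being added unsplit, on a stable PF-burnout correlation of -0.3 to -0.7, and on a 0.5 SD gain in PF. They show which extension to avoid, not what the plan will do.

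This should be fixed. It concerns a stated aim, but hypotheses 1 and 3 and the primary burnout comparison are unaffected.

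**What to change.** Keep the stated mixed model for hypotheses 1 and 3 and for the arm-to-PF path. For hypothesis 2, state an indirect effect for app versus waiting list:

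1. Path a: follow-up minus baseline PF, regressed on arm.
2. Path b: follow-up minus baseline outcome, regressed on arm and change in PF. Equivalently, use a mixed model with PF split into person-mean and within-person parts and take the within-person slope.
3. Report a × b with a bootstrap confidence interval.
4. Say that PF will not be entered as a single unsplit time-varying covariate.
5. Add a sensitivity analysis showing how strong a time-varying common cause of PF and outcome would have to be to explain the indirect effect.
6. Word the mediation statements in the abstract's Conclusions and in the Discussion to match: with mediator and outcome measured together at two time points, a positive result is consistent with mediation but does not establish PF as the mechanism.

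The cost is a few sentences in the plan and modest analysis work. All the measures are already in Table 1. The price is a less precise path b, because between-person information is no longer borrowed. The Results section says data collection is complete, so record whether this choice was made before the outcome data were examined.

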### PF Training and Medical Student Burnout and Well-being

The literature has demonstrated associations between PF and burnout and well-being outcomes and evidence for the relevance of these processes to medical student and physician burnout and well-being. On this basis, we expect that training medical students to develop PF skills will have positive benefits concerning burnout and well-being. Given the absence of intervention studies with this population where all 6 PF processes are trained, we will assess the efficacy of our purpose-developed app-based ACT intervention for medical students. Stage 1 of the intervention will deliver a brief educational module that provides a conceptual explanation of each of the 6 PF processes as well as self-reflection and experiential skill practice activities.

Hypothesis 1 states the following: on the basis of the theoretical background presented, we hypothesize that medical students in the individualized and nonindividualized intervention groups will demonstrate significantly greater improvements in PF, burnout, and well-being outcomes (before and after intervention) compared with those in a waiting-list control group.

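### The two-time-point random-intercept model most naturally tests a change contrast; a common baseline mean, or T2 adjusted for T1, would cut the variance by about 15 to 20% at no cost

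*Protocol article*

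**What the plan says.** The Data Analysis section of the protocol article plans mixed models for Hypotheses 1 to 3, "including a random intercept for participants to account for repeated measures". It lists no fixed effects and does not say how baseline enters. Four other places bear on the reading:

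- Data Collection Tools and Procedures (and Table 1): burnout, well-being, psychological flexibility and the depression, anxiety and stress scale are measured at T1 and T2 only.
- Sample Size: the calculation sought an "appropriate sample size for a repeated measures multivariate analysis of variance", with "3 groups; measuring 2 time points [baseline and after the intervention" as the layout and a "high correlation between pre- and postintervention measures, 0.6".
- Hypothesis 1 expects that "medical students in the individualized and nonindividualized intervention groups will demonstrate significantly greater improvements in PF, burnout, and well-being outcomes" from before to after the intervention, relative to the waiting list. Hypothesis 3 uses the same form for individualized against nonindividualized.
- Study Design and Intervention Stages place randomization after a brief educational session, and the Attrition list puts the T1 assessments ahead of that session.

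**The concern.** A random intercept that handles repeated measures needs at least two outcome rows per participant. With one post-baseline visit, T1 has to be one of them. The power calculation treats baseline as a level of the time factor, and the hypotheses speak of improvement. So the natural model gives each arm its own baseline mean and tests arm by time. With two visits, that test compares mean change between arms.

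If T1 precedes randomization, any baseline difference between arms is chance. A model with free baseline means estimates those differences and carries them into the effect. A model that uses the common baseline mean does not, and is more precise at any correlation below 1. Precision is scarce here: the trial is small and allows for 30% loss, and its own Limitations section warns that weak stage 2 engagement would hinder the individualized versus nonindividualized comparison. The Results section reports recruitment and data collection as complete, so sample size can no longer be raised. The analysis model is the lever that remains.

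**Working it through.** **Inputs.** From Sample Size: three arms, two time points, ρ = 0.6, 80% power, α = 0.05 (labelled Cronbach α there, read as the significance level), effect size 0.25, required total 117, recruitment 153, attrition up to 30%. Completers: 153 × 0.7 = 107.1, or n = 35.7 per arm out of N = 51 randomized per arm. Assumption: 0.25 is Cohen's f on the T2 standard deviation σ, since the article does not define the scale.

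**The plan's own figure.** The article says "the total required sample size is 117 (39 per intervention arm"). The between-groups repeated-measures formula is λ = f²·N_total·m / [1 + (m − 1)ρ], with 2 and N_total − 3 df.

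- m = 2: λ = 0.0625 × 2 / 1.6 × N_total = 0.078125 N_total. At 117 the power is 76.6%, and 127 are needed (129 in equal arms).
- m = 3: 117 gives 80.3%.
- The within-between interaction formula, λ = f²·N_total·m / (1 − ρ) with m = 2, needs only 36.

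So 117 does not follow from two time points. That is a separate matter, but it means 117 is not a secure 80% starting point on this reading of f.

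**Variance per arm among complete pairs, in units of σ²/n.**

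- Change contrast: 2(1 − ρ) = 2 × 0.4 = 0.80.
- T2 adjusted for T1, or common baseline mean: 1 − ρ² = 1 − 0.36 = 0.64.
- Ratio 0.64 / 0.80 = 0.80: a 20% cut, confidence intervals 10.6% narrower (√0.80 = 0.894), equal to 1 / 0.80 = 1.25 times the participants.

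**Variance per arm under 30% attrition, likelihood fit.** A mixed model also uses participants who have T1 only.

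- Free baseline means: (1 − ρ²)/n + (1 − ρ)²/N = 0.64/35.7 + 0.16/51 = 0.02106.
- Common baseline mean: (1 − ρ²)/n = 0.64/35.7 = 0.01793.
- Ratio 0.851: a cut of about 15%, intervals 7.7% narrower (√0.851 = 0.923), equal to about 17.5% more participants.

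A simulation of 400 trials (51 per arm, 30% of T2 missing at random) gave ratios of 0.79 for adjusted against completer change and 0.87 for constrained against free-baseline mixed model, close to the theoretical 0.80 and 0.85.

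**Omnibus power (2 df), f = 0.25, 107 completers.** λ = 3f² / (variance per arm).

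| Analysis | λ at ρ = 0.6 | Power, ρ = 0.5 | Power, ρ = 0.6 | Power, ρ = 0.7 |
|---|---|---|---|---|
| Completer change score | 8.37 | 62% | 72% | 85% |
| Mixed model, free baseline | 8.90 | 66% | 75% | 86% |
| Common baseline or adjusted | 10.46 | 75% | 82% | 90% |

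**Pairwise power, ρ = 0.6, unadjusted two-sided α = 0.05, normal approximation.** Power = Φ(d / √(2v) − 1.96), with v the variance per arm.

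| d | Completer change | Mixed model, free baseline | Common baseline or adjusted |
|---|---|---|---|
| 0.25 | 22% | 23% | 26% |
| 0.50 | 66% | 68% | 75% |
| 0.53 | 71% | 73% | 80% |
| 0.612 | 82% | 85% | 90% |

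For orientation, f = 0.25 corresponds to d = 0.25 × 3/√2 = 0.53 for each active arm against waiting list if the two active arms are equal. It corresponds to d = 0.25 × √6 = 0.612 between the extreme arms if the three means are evenly spaced.

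**The case against.** The strongest reply is that the criticised model is not written down. The Data Analysis section names a random intercept and nothing else about the mean structure. A model with time and arm × T2 but no arm main effect fits those words too, and a condensed article may leave baseline handling to an analysis plan that is not shown. This stands in part. The free-baseline reading is an inference from the two visits, the repeated-measures sizing and the improvement hypotheses, and the text cannot be said to specify it.

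The second reply also stands: the difference in mean change is a valid estimate under randomization and answers the hypotheses as worded. A reader might infer bias or a wrong analysis, but the article supports neither.

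The third reply concerns size, and it limits three tempting claims:

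- A reader might apply the 20% cut to the mixed model after attrition. It holds for complete pairs; against a likelihood fit that keeps T1-only participants, the cut is about 15%.
- A reader might conclude that the change restores 80% power. On the stated inputs 117 gives 76.6% before any loss, so there was no 80% to restore. The 82% also depends on the undefined effect-size scale: with f on the interaction scale, power exceeds 99% either way.
- A reader might carry the omnibus figure over to Hypothesis 3. That is a two-arm contrast, and at d = 0.50 or below it stays under 80% with the better model.

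None of this removes the recommendation. Where T1 precedes randomization, the common baseline mean holds by design and the gain in precision costs nothing.

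**Conclusion.** The point holds as an efficiency recommendation. On the natural reading, the planned arm-by-time test is a change contrast, and at ρ = 0.6 it has 1.25 times the variance of a baseline-adjusted contrast among complete pairs, or about 1.17 times when T1-only participants are kept. The gain shrinks as ρ rises: the complete-pair ratio is (1 + ρ)/2, so the cut is 25% at ρ = 0.5 and 15% at ρ = 0.7.

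The variance result rests on ρ, equal variances at T1 and T2, a continuous outcome scale, and T1 preceding randomization. The last is read from the order of steps in the text, since the timeline figure is not shown. The power figures rest further on 30% attrition with T2 missing at random, on Cohen's f on the T2 standard deviation, and on the 2-df omnibus test. They should not be quoted for the pairwise hypotheses.

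**What to change.** For each T1/T2 outcome analysed on a continuous scale, specify one of two models before analysis:

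- a mixed model with a common baseline mean (fixed effects for time and arm × T2, no arm main effect) and an unstructured 2 × 2 covariance; or
- T2 regressed on arm with T1 as a covariate.

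Take the T2 arm contrasts as the estimates for Hypotheses 1 and 3. State in the text that T1 is completed before randomization, as this justifies the constraint. If an analysis plan already says this, a sentence in the article pointing to it is enough.

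The cost is one line of model specification, with no new data. Choosing the model in advance also rules out a later choice between change-score and baseline-adjusted results, which can differ in a trial of this size.
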